### 6.2.2 Recruitment and trial procedures

A flyer, which includes a general overview of the study and contact details, will be sent via e-mail to the patients of the participating MS Centres by the MS Centre team. People who show interest in participating in the study will be contacted by the study coordinator or centre Principal Investigator (PI). Subsequently, one trained clinical psychologist (Italian READY for MS facilitator) makes an appointment with those patients who met the inclusion criteria and agreed to participate in the study, and checks all eligibility criteria. She/he sends an e-mail to the participant with the link to the website containing the set of questionnaires. The total assessment will last about 55 minutes in each time-points (additional 20 minutes at T1 and T2 for filling in the satisfaction questionnaire). Each centre will collect information on the number of people approached, screened, and eligible prior to random assignment, with reasons for non-enrolment. Participants will be then assigned to the Italian READY for MS or control condition. Randomization will be provided by an independent randomization unit, using computer-based cluster randomization with minimization [49] (2 factors: Centre and CDRISC score  $< 50$  and  $\geq 50$ ). Groups will be allocated to Italian READY for MS or control intervention in a 1:1 ratio. Confirmation e-mails will be sent to the study coordinator and centre PI. The interventions will start within two weeks of the baseline assessment.

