## **6.3 Interventions**

Each group will be composed of 8-10 participants, a total of 8 groups will be performed (four Italian READY for MS and four relaxation); within each arm, the groups will be homogeneous assembled so that PwMS will be as much homogeneous as possible in terms of CD-RISC 25 scores. The Italian READY for MS groups will be run by a psychologist of the “Rete Psicologi AISM” who participated and successfully completed “The ACT and be READY for MS training program”. To

limit possible involuntary contaminations, the control group will be run by a psychologist not involved in “The ACT and be READY for MS training program” and with no expertise in ACT or mindfulness interventions. Each group will be run in a dedicated room of the Hospital/Institute of each participating MS Centre. Participants will be asked not to disseminate information or materials of the program in which they are allocated. In addition, READY for MS and relaxation groups will be scheduled in order to prevent contact between participants of the two groups. Facilitators will be asked not to disseminate information or materials with the colleagues who are running the other intervention.

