## 6.5 Data analysis

### 6.5.1 Sample size calculation

The sample size calculation was based on the results from the pilot study [paper under review], where we found a mean change in the CD-RISC 25 at 3-month follow-up in the READY for MS arm equal to 15.61 (standard deviation, SD: 13.63, n=18) vs. a mean change in the relaxation arm equal to 5.95 (SD: 14.11, n=19). Moreover, we estimated an intra-cluster correlation coefficient (ICC) equal to 0.08.

A sample size of 12 clusters per treatment arm (total number of clusters=24) with 10 individuals per cluster (total sample size 240) achieves 94.6% power to detect a mean difference of 9.66 between the two arms in terms of change in CD-RISC 25 at 3-month follow-up [59]. The SD of change in the CD-RISC 25 at 3-month is assumed equal to 14.53. The ICC is assumed, conservatively, equal to 0.10. The type I error (alpha) is assumed to 0.05.

Starting from the previous scenario (i.e. total sample size 240, 24 clusters, 10 subjects per cluster), we computed the study power assuming three scenarios of drop-out.

#### Scenario 1

Assuming a drop-out of 20% uniformly distributed among clusters (i.e. two individuals lost within each cluster): 12 clusters per treatment arm (total number of clusters=24) with eight individuals per cluster (total sample size 192) achieves 92.1% power to detect a mean difference of 9.66 between the two arms in terms of change in CD-RISC 25 at 3-month follow-up [59]. The SD of change in the CD-RISC 25 at 3-month is assumed equal to 14.53. The ICC is assumed, conservatively, equal to 0.10. The type I error ( $\alpha$ ) is assumed to 0.05.

#### Scenario 2

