### 6.5.2 Statistics

Descriptive statistics will be calculated for general and clinical variables. Specifically, continuous variables will be summarised by their mean and SD, or median and interquartile range; categorical variables will be summarised as numbers and percentages.

The normality assumption will be tested with the Shapiro-Wilk test. Between-group comparisons will be carried out using either the two-sided unpaired t-test or the Wilcoxon two sided two-sample test for continuous variables depending on data distribution, and the chi-squared test for categorical variables. Correlations will be computed using Spearman's or Pearson's coefficients depending on data distribution.

Our primary end-point is the between-arm difference in T0 - T2 changes in CD-RISC 25 score.

Longitudinal changes will be analyzed using repeated measures hierarchical (patients nested in clusters) generalized linear mixed models, accounting for the cluster effect (using a random intercepts for clusters). To mitigate the potential risk of inflating the type I error in presence of a small number of clusters, we will use the Kenward-Roger degrees of freedom correction, which does not rely on the assumption of fixed cluster sizes [60].

All group comparisons will be carried out according to the intention-to-treat principle, i.e. participants will be analysed in the arm (READY for MS or relaxation) to which they were randomized. In addition, we will: carry out a per protocol analysis; assess the sensitivity of the results to excluding patients who missed three or more READY for MS group sessions. No interim analysis has been planned.

Inter-rater reliability will be assessed with the weighted kappa statistic for ordinal data, and the ICC for continuous data [61-63]; 95% confidence intervals (CIs) will be determined using the bootstrap method (1000 replications).

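### Groups are minimised on centre and CD-RISC and sorted on baseline CD-RISC, but the primary model names neither as a covariate and the power calculation ignores the sorting

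*Protocol*

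**What the plan says.** Three parts of the protocol bear on this point.

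- **Allocation (6.2.2).** Groups are randomised "using computer-based cluster randomization with minimization [49] (2 factors: Centre and CDRISC score", the score being split at 50.
- **Group formation (6.3).** Within each arm, "groups will be homogeneous assembled so that PwMS will be as much homogeneous as possible in terms of CD-RISC 25 scores". This is the baseline of the primary outcome, the T0-T2 change in CD-RISC 25.
- **Analysis (6.5.2).** "Longitudinal changes will be analyzed using repeated measures hierarchical (patients nested in clusters) generalized linear mixed models", with a random intercept for clusters and Kenward-Roger degrees of freedom. No fixed effects are listed, so neither centre nor baseline CD-RISC appears. Nothing excludes them either.

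Section 6.5.1 states that twelve clusters per arm "with 10 individuals per cluster (total sample size 240) achieves 94.6% power to detect a mean difference of 9.66 between the two arms". "The SD of change in the CD-RISC 25 at 3-month is assumed equal to 14.53". "The ICC is assumed, conservatively, equal to 0.10", against a pilot estimate of 0.08 (section 2.1 gives .07). The section does not mention the sorting and does not describe the ICC as baseline-adjusted.

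**The concern.** Low scorers have more room to rise and regress towards the mean, so baseline CD-RISC should predict change. Making groups alike on baseline then makes them differ from one another in mean change. The between-group variance of change rises, and with it the ICC that drives the power of a trial with 24 clusters. The power calculation takes 0.10 without allowing for a step that the protocol itself orders.

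What is at stake is precision and power. Baseline CD-RISC is already collected, because eligibility and minimisation both need it, so a model that uses it recovers the loss without new data. Naming the covariates in advance also removes a choice that could otherwise be made after seeing the data.

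**Working it through.** **Inputs from the protocol.** Difference 9.66, SD of change 14.53, ICC 0.10, k = 12 clusters per arm with m = 10 (all from 6.5.1); "The type I error (alpha) is assumed to 0.05". The power section does not state sidedness; I take it as two-sided, as in 6.5.2 ("using either the two-sided unpaired t-test or the Wilcoxon two sided two-sample test"). I use the 24 clusters of 6.5.1. Section 6.3 gives eight groups in total, which must be reconciled separately.

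**Step 1: reproduce the stated power.** SE = SD × √[2(1 + (m − 1)ICC)/(km)], two-sided noncentral t with 2(k − 1) = 22 df.

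- m = 10: 14.53 × √(2 × 1.90/120) = 2.586; 9.66/2.586 = 3.736; power 94.6% (stated 94.6%).
- m = 8: 14.53 × √(2 × 1.70/96) = 2.734; 9.66/2.734 = 3.533; power 92.1% (stated 92.1%).
- m = 7.5: 14.53 × √(2 × 1.65/90) = 2.782; 9.66/2.782 = 3.472; power 91.3% (stated 91.8%, by simulation with unequal cluster sizes).

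**Step 2: how far baseline predicts change.** The T0-T2 correlation r is not in the protocol; I assume 0.3 to 0.7 with equal variances. The squared correlation of baseline with change is (1 − r)/2, which is 0.35, 0.25 and 0.15 for r = 0.3, 0.5 and 0.7. Sorting can move part of that share into the between-group component. Adjustment removes it from the error.

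**Step 3: how much ICC the plan can absorb.** From the formula in step 1, power falls to 90% at an ICC of 0.145 (m = 10), 0.120 (m = 8) or 0.112 (m = 7.5). It falls to 80% at 0.23, 0.21 or 0.20.

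**Step 4: simulation.** Further assumptions: group variance apart from sorting equal to 0.10 of the variance of change; eight centres as listed in 6.1, of which four have two groups per arm and four have one (12 groups per arm); no centre effect. Sorting takes place inside each centre and arm. Both analyses compare group means on 22 df, one of raw change and one of baseline-adjusted change. There were 3,000 simulated trials for power and 2,000 for type I error.

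| m | r | ICC of change after sorting | Power, unadjusted | Type I error, unadjusted | Power, adjusted |
|---|---|---|---|---|---|
| 8 | 0.3 | 0.25 | 80.7% | 0.013 | 96.6% |
| 8 | 0.5 | 0.21 | 83.4% | 0.019 | 95.3% |
| 8 | 0.7 | 0.16 | 87.2% | 0.026 | 94.1% |
| 10 | 0.3 | 0.25 | 83.6% | 0.009 | 97.5% |
| 10 | 0.5 | 0.21 | 87.3% | 0.017 | 96.5% |
| 10 | 0.7 | 0.16 | 89.9% | 0.023 | 96.1% |

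The unadjusted test is conservative because both arms contain low and high groups. Sorting inflates the estimated standard error but not the true variability of the arm difference. This is also why simulated power exceeds the closed form at the same ICC (75.6% at m = 8 and ICC 0.25).

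With sorting across a whole arm, the extreme case, unadjusted power at m = 8 is 60.5%, 71.4% and 79.8% for r = 0.3, 0.5 and 0.7. Adjusted power stays at about 94-97%.

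**The case against.** A reader might infer that the sponsor has chosen an unadjusted analysis. The protocol does not say so. Section 6.5.2 gives a model class and lists no fixed effects at all, not even arm or time; covariates are commonly left to the SAP, which is not shown. This objection stands, so the point is that the model names neither factor. It does not dispose of the matter, because the mismatch between sorting in 6.3 and the ICC in 6.5.1 lies wholly inside the protocol.

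A reader might also infer that the planned power is undone. That needs a near worst-case layout. Groups run at the centres, and 12 groups per arm over eight centres is about 1.5 per arm per centre. A centre with one group per arm cannot sort. The plan also has margins: its SD of 14.53 exceeds the pooled pilot SD of 13.88 (from 13.63 with n = 18 and 14.11 with n = 19), and its ICC exceeds the pilot's. If the pilot groups were sorted too, which the protocol does not say, the pilot ICC already holds part of the effect. These points stand: power is eroded, not lost.

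Nor can it be said that omitting the covariates widens the confidence interval under every reading of the model. If T0 is one of the outcomes and only cluster and patient intercepts are random, group-level variation in change is not modelled. The standard error is then too narrow, and simulated type I error was about 12-17%, with or without sorting. That is a separate weakness of the model text. The power loss shown here applies to an analysis of change that respects the clusters.

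Finally, the effect of omitting centre cannot be sized, because no centre variance is given, and minimisation on CD-RISC already limits chance imbalance in baseline.

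**Conclusion.** The point holds as a nearly free improvement. Under the assumptions in the working, with sorting inside centres and 8 per group, an unadjusted analysis of change has about 81-87% power against the stated 92.1%, with a type I error of about 0.01-0.03. Baseline adjustment gives about 94-97%. The direction is firm whenever baseline predicts change. The size rests on the T0-T2 correlation and the group layout, neither of which the protocol gives. Power clearly below 80% appears only with arm-wide sorting. The case for naming centre rests on its being a minimisation factor, not on a calculated gain.

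**What to change.** **Section 6.5.2.** Name baseline CD-RISC 25 (continuous, patient level) and centre as covariates in the primary model, with centre random, or fixed. Give each secondary outcome its own baseline as covariate.

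**Section 6.5.1.** Either say that the stated power presumes the baseline-adjusted analysis and that 0.10 is an assumption for the ICC on that scale, or justify 0.10 for unadjusted change when groups are sorted. The text should not claim that the pilot ICC was baseline-adjusted, because the protocol reports it beside unadjusted mean changes.

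**Cost.** Wording only, with no new data. Fixed effects for eight centres use up to 7 of the 22 group-level df, leaving 15. With 7.5 per group, r = 0.5-0.7 and an ICC of 0.10 on the adjusted scale, that moves adjusted power from 94.9-96.9% to 94.0-96.3%. A random centre effect is an option if those df are wanted.

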### 6.3.1 Italian READY for MS

READY for MS is an adult ACT informed group resilience training program which consists of seven weekly 2.5 hour sessions plus a 2.5 hour ‘booster’ session approximately five weeks after the seventh session (S2 Appendix - READY for MS sessions). Content of the seven weekly sessions is as follows: an introductory module (Introduction to the READY Resilience Model), five modules focusing on each of the six ACT processes (Mindfulness, Acceptance, Cognitive Defusion, Self-as-Context, Values and Meaningful Action), and a review module (Review and Future Planning). The booster session provides a review of the program content. The program has a facilitator manual, participant workbook, and audio recordings of mindfulness exercises. Throughout the program, participants are encouraged to share their progress and experience of applying the READY strategies and techniques. It incorporates a blend of psychoeducation and experiential exercises, combined with readings and homework exercises that participants are encouraged to practice between sessions [30].

### 6.3.2 Control intervention

The control condition consisted of a group relaxation program based on autogenic training [50]. The intervention consisted of seven, 1-hour weekly group sessions, followed by a ‘booster’ session approximately after five weeks (S3 Appendix - Relaxation sessions). This control program matched the study intervention in number of sessions and schedule (but not in session content and length) in order to control for the non-specific effects of Italian READY for MS. The program had a facilitator manual, participant workbook, and audio recordings of relaxation exercises.

##### 6.4.1 Primary Outcome Measure

Resilience. The CD-RISC 25 is used to assess psychological resilience. It is composed of 25 items, each rated on a 5-point scale (0-4), with higher scores reflecting greater resilience. The scale demonstrated good psychometric properties [39].

##### 6.4.2 Secondary Outcomes

Mood

- The HADS is a well-validated measure that consists of two seven-item subscales to assess anxiety and depressive levels. Higher scores indicate higher levels of depressive or anxiety symptoms [40]. Unlike many similar measures, the HADS excludes somatic symptoms of anxiety and depression, which may overlap with physical illness [40].
- PANAS consists of two 10-item mood scales and it is a self-report measure of positive and negative affect. Respondents are asked to rate the extent to which they have experienced each particular emotion within a specified time period, with reference to a 5-point scale. The scale point are: 1 ‘very slightly or not at all’, 2 ‘a little’, 3 ‘moderately’, 4 ‘quite a bit’ and 5 ‘very much’. The PANAS resulted to be a reliable and valid measure of the constructs it was intended to assess [41]

Health related quality of life.

- The MSQOL-54 is a health-related QoL measure that comprises the generic Short-Form 36-item (SF-36), plus 18 MS-specific items [42]. The 54 items are organized into 12 multi-item and two single item subscales. As for the SF-36, two composite scores (Physical Health Composite, PHC, and Mental Health Composite, MHC) are derived by combining scores of the relevant subscales. The MSQOL-54 has well documented validity in terms of content, constructs, reliability [42], discrimination and responsiveness [57]. To limit multiple comparisons, we primarily assessed changes in the MHC.
- The EQ-5D-3L is a preference-based health-related QoL measure with one question for each of the five dimensions that include mobility, self-care, usual activities, pain/discomfort, and anxiety/depression. It also includes a Visual Analog Scale (VAS), to report perceived health status with a grade ranging from 0 (the worst possible health status) to 100 (the best possible health status) [43].

### Well-being

MHC-SF measures positive mental health and comprises 14 items, representing various feelings of well-being. Respondents rate the frequency of every feeling in the past month on a 6-point Likert scale (never, once or twice a month, about once a week, two or three times a week, almost every day, every day). The MHC-SF has shown good psychometric properties [44].

### General measure of ACT processes

The 23-item CompACT has three subscales: openness to experience (OE), behavioral awareness (BA), valued action (VA). A total score is calculated by summing the three subscale scores. Items are rated on a 7-point Likert scale. The full-scale CompACT total score ranges from 0-138, with higher scores indicating greater psychological flexibility. The CompACT demonstrated good internal consistency, and converged and diverged in theory-consistent ways with other measured variables: higher levels of psychological inflexibility were associated with higher distress and lower health and well-being [45].

### Clinical information and measures

The following information will be also provided by the PwMS neurologist at T0: EDSS score [58], MS course (relapsing remitting, primary progressive, secondary progressive), presence/type of co-pathologies, and ongoing treatment. The neurologist will update occurrence of new relapses at each time-point.

### Satisfaction with the intervention

Four purpose-build questionnaires (two for Italian READY for MS; two for relaxation) explore the satisfaction with the Italian READY for MS program or relaxation.

- “Satisfaction with the Italian READY for MS – T1” questionnaire is composed of four sections: 1) Usefulness of the Italian READY for MS program in promoting the six protective factors of resilience (5-item); 2) Overall evaluation of the Italian READY for MS program (6-item); 3) Satisfaction with the READY Personal Plan (5-Item); 4) Participants personal experience with the Italian READY for MS (8-open questions on their experience).

- “Satisfaction with the Italian READY for MS – T2” questionnaire is composed of three sections: 1) Usefulness of the Italian READY for MS program in promoting the six protective factors of resilience (5-item). 2) Overall evaluation of the Italian READY for MS program (6-item); 3) Participants personal experience with the Italian READY for MS (10-open questions on their experience).
- “Satisfaction with the relaxation program – T1” questionnaire is composed of two sections: 1) Overall evaluation of the relaxation program (5-item); 2) Satisfaction with the relaxation Personal Plan (5-Item).
- “Satisfaction with the relaxation program – T2” questionnaire is composed of 5-item and 2 open ended questions on the overall evaluation of the relaxation program.

#### Adherence to the intervention

The facilitator collect information on participant’s retention and ask the participants to rate the level of commitment with the homework activities (READY Personal Plan; Relaxation Personal Plan), after each session.

#### Intervention fidelity

- The Session Fidelity Checklist is a purpose-build checklist that reflects the sequences of session components as reported in the Facilitator Manual. It also includes a section for clinical notes. Two versions are available, one for the Italian READY for MS (S4 Appendix – READY for MS Session Fidelity Checklist), and one for the relaxation program (S5 Appendix – Relaxation Session Fidelity Checklist).
- “The Acceptance and Commitment Therapy Fidelity Measure (ACT-FM)” is 25-item checklist on a 4-point Likert scale that evaluates the adherence with the ACT therapeutic style. It is composed of two total scores (Total ACT Consistency Score (0-36) = Total ACT Inconsistency Score) and eight subscales that range from 0 to 9, namely: 1) ACT Consistent Therapist Stance; 2) ACT Inconsistent Therapist Stance; 3) ACT Consistent Open Response Style; 4) ACT Inconsistent Open Response Style; 5) ACT Consistent Aware Response Style; 6) ACT Inconsistent Aware Response Style; 7) ACT Consistent Engaged Response Style; 8) ACT Inconsistent Engaged Response Style [51].

## 6.5 Data analysis

### 6.5.1 Sample size calculation

The sample size calculation was based on the results from the pilot study [paper under review], where we found a mean change in the CD-RISC 25 at 3-month follow-up in the READY for MS arm equal to 15.61 (standard deviation, SD: 13.63, n=18) vs. a mean change in the relaxation arm equal to 5.95 (SD: 14.11, n=19). Moreover, we estimated an intra-cluster correlation coefficient (ICC) equal to 0.08.

A sample size of 12 clusters per treatment arm (total number of clusters=24) with 10 individuals per cluster (total sample size 240) achieves 94.6% power to detect a mean difference of 9.66 between the two arms in terms of change in CD-RISC 25 at 3-month follow-up [59]. The SD of change in the CD-RISC 25 at 3-month is assumed equal to 14.53. The ICC is assumed, conservatively, equal to 0.10. The type I error (alpha) is assumed to 0.05.

Starting from the previous scenario (i.e. total sample size 240, 24 clusters, 10 subjects per cluster), we computed the study power assuming three scenarios of drop-out.

#### Scenario 1

Assuming a drop-out of 20% uniformly distributed among clusters (i.e. two individuals lost within each cluster): 12 clusters per treatment arm (total number of clusters=24) with eight individuals per cluster (total sample size 192) achieves 92.1% power to detect a mean difference of 9.66 between the two arms in terms of change in CD-RISC 25 at 3-month follow-up [59]. The SD of change in the CD-RISC 25 at 3-month is assumed equal to 14.53. The ICC is assumed, conservatively, equal to 0.10. The type I error ( $\alpha$ ) is assumed to 0.05.

#### Scenario 2

We assumed a variables drop-out of 20% (e.g. 5% failure to reach the enrollment target of 10 participants per group and 15% drop-out during intervention/follow-up) among clusters (i.e. 0 individuals lost within two clusters, one individual lost within five clusters, two individuals lost within eight clusters, three individuals lost within nine clusters). Since no exact formula exists for such a scenario, we performed a simulation study. We simulated 24 (number of clusters) times ten observations (subjects) from a normal distribution with mean equal to 9.66, SD equal to 14.53 and ICC=0.10. Then we randomly selected five clusters where we deleted randomly one subject, we randomly selected eight clusters where we deleted randomly two subjects each, we randomly selected nine clusters where we deleted randomly three subjects each. We simulated 1000 samples and computed the observed statistical power. Twelve clusters per treatment arm (total number of clusters=24) with 10 individuals in two clusters, nine individuals in five clusters, eight individuals in eight clusters, and seven individuals in the remaining nine clusters (total sample size 192) achieves 92.0% power to detect a mean difference of 9.66 between the two arms in terms of change in CD-RISC 25 at 3-month follow-up [59].

#### Scenario 3

We assumed a variables drop-out of 25% (e.g. 10% failure to reach the enrollment target of 10 participants per group and 15% drop-out during intervention/follow-up) among clusters (i.e. 0 individuals lost within one clusters, one individual lost within one clusters, two individuals lost within seven clusters, three individuals lost within 15 clusters). Since no exact formula exists for such a scenario, we performed a simulation study. We simulated 24 (number of clusters) times ten observations from a normal distribution with mean equal to 9.66, SD equal to 14.53 and ICC=0.10. Then we randomly selected one cluster where we deleted randomly one subject, we randomly selected seven clusters where we deleted randomly two subjects each, we randomly selected 15 clusters where we deleted randomly three subjects each. We simulated 1000 samples and computed the observed statistical power. Twelve clusters per treatment arm (total number of clusters=24) with 10 individuals in one cluster, nine individuals in one cluster, eight individuals in seven clusters, and seven individuals in the remaining 15 clusters (total sample size 180) achieves 91.8% power to detect a mean difference of 9.66 between the two arms in terms of change in CD-RISC 25 at 3-month follow-up [59].

